## Abstract

**Aim:**

This study aims to evaluate the effects of preoperative stoma simulation on preoperative state anxiety and postoperative stoma adaptation among individuals scheduled for stoma surgery.

**Design:**

This study is designed as a two‐arm, parallel‐group randomized controlled trial.

**Methods:**

A total of 52 patients scheduled for stoma surgery will be randomly allocated to either the intervention group (*n* = 26) or the control group (*n* = 26). The intervention group will receive a structured preoperative stoma simulation in addition to standard care, whereas the control group will receive standard preoperative care alone. The primary outcome is preoperative state anxiety, which will be measured using the Spielberger State Anxiety Inventory 24 h before surgery and on the morning of surgery. The secondary outcome is postoperative stoma adaptation, which will be assessed at discharge and 1 month after surgery using the Ostomy Adjustment Inventory. Data will be collected through face‐to‐face interviews. Outcome assessments will be conducted by a blinded assessor, and statistical analyses will be performed by a blinded statistician.

**Results:**

As this manuscript presents the study protocol, the results are not yet available. The findings are expected to provide evidence regarding the effectiveness of preoperative stoma simulation in reducing anxiety and improving postoperative adaptation.

**Conclusion:**

This trial is expected to provide evidence regarding the effectiveness of preoperative stoma simulation on preoperative state anxiety and postoperative stoma adaptation and may contribute to the development of evidence‐based nursing interventions for individuals undergoing stoma surgery.

**No Patient or Public Contribution:**

Patients or the public were not involved in the design, conduct, reporting, or dissemination plans of this research.

**Trial Registration:**

ClinicalTrials.gov Identifier: NCT06737887. Registered on December 11, 2024

## Introduction

1

Colorectal cancer (CRC) is among the most common malignancies worldwide and ranks third among cancer‐related causes of death (Polat et al. 2021). According to the Global Cancer Statistics Report (Globocan, 2020 edition), there are an estimated 1.9 million new cases of CRC and 930,000 deaths. The incidence rate is highest in men in Australia/New Zealand at 40.6 per 100,000 and lowest in women in several African regions and South Asia at 4.4 per 100,000. The mortality pattern for this cancer type is similar to that of incidence (Sung et al. 2021; Morgan et al. 2023). The burden of CRC is projected to increase by an average of 45% in incidence and mortality by 2040, with the majority of cases in countries with high or very high human development indices (HDIs) (Xi and Xu 2021).

It is estimated that an average of 725,000–1,000,000 people in the U.S. (UOAA 2024) and 13,500 people in the UK (Nazarko 2024) live with a stoma. Stoma surgery, which is frequently used in treating patients with colorectal cancer, contributes significantly to the economy by prolonging life expectancy, improving health outcomes, and improving quality of life (Zewude et al. 2021). Health professionals should support patients' adaptation to the stoma by providing stoma‐related education and skill training, thereby enhancing self‐care knowledge, self‐care performance, and independence in stoma management (Momeni Pour et al. 2023). There is evidence that preoperative training can help patients adapt well to the process after surgery, reduce physical and psychological problems, and shorten the duration of hospitalization (Hughes et al. 2020; Brodersen et al. 2023).

## Background

2

Stoma is a medical and social problem worldwide. Approximately 100,000 patients undergo stoma surgery annually in the United States (Ferrara et al. 2019). Although stoma surgery is considered a therapeutic approach in individuals with colorectal cancer, it causes the loss of voluntary bowel control and privacy, and the unnoticed excretory process becomes visible and noticeable (Ayik et al. 2018; Duluklu and Çelik 2019).

In this surgical intervention, which changes the excretory mechanism direction and the functionality of existing muscles, individuals gain various physiological, psychological, and social experiences (Liu et al. 2024). These experiences, starting from the preoperative period, affect the postoperative colostomy adaptation process and the general quality of life and lead to positive or negative outcomes (Ayik et al. 2018; Duluklu and Çelik 2019). Therefore, it is important to determine the appropriate nursing interventions for patients with colostomy to cope with and adapt to current physical changes.

Despite the development of surgical intervention techniques and disposable care products for stoma care, stoma‐related complications account for an average of two‐thirds of cases (Ferrara et al. 2019). In the development of complications, stoma type, region, failure to mark the surgical site, failure to determine the region well, emergency surgery, inadequate preoperative preparation and postoperative care, failure to manage anxiety, and other comorbid conditions affect the patient (Chan et al. 2023; Altintas et al. 2025).

Individuals with a stoma require education and counselling both before and after surgery to effectively manage stoma‐related care and successfully adapt to life with a stoma (Akbayrak and Uslu 2026). Patient education should start with the first admission to the clinic; accurate information about the procedures should be conveyed to patients and their relatives understandably. It was determined that 36% of patients scheduled for stoma surgery did not receive preoperative marking, and 6% developed parastomal hernia complications (Kozan and Gültekin 2018). Marking the area before stoma surgery reduces the likelihood of potential stoma problems such as leakage, bag insertion difficulties, associated skin irritation and pain, and improves the quality of life of patients in the postoperative period (Gök et al. 2019).

On the basis of this information, simulating this artificial organ while the patient spends a day with a stoma bag before elective surgery, where he/she performs the actions of sitting, getting up, walking, going to the toilet, dressing, and communicating, can regulate the patient's anxiety, allow him/her to ask the nurse for help with difficulties, and improve the postoperative adaptation process.

The hypotheses of the study are as follows:
*Stoma simulation intervention reduces patients' preoperative anxiety*.

*Stoma simulation intervention increases patients' adaptation to the stoma after surgery*.

## Method

3

### Trial Status

3.1

This trial was registered at ClinicalTrials.gov (Registration number: NCT06737887) on December 11, 2024. The current protocol version is Version 1.0 (January 2, 2027). Participant recruitment is planned to begin on January 2, 2027, and it is expected to be completed by January 2, 2028.

### Design

3.2

This study will be a two‐arm, parallel‐group randomized controlled trial with blinded outcome assessment and blinded data analysis in patients scheduled for stoma surgery. The aim of this study is to evaluate the effects of preoperative stoma simulation on patients' anxiety levels and postoperative stoma adaptation. Patients who meet the inclusion criteria and agree to participate in the study will be randomized to the stoma simulation (intervention group) or control group. The application will be performed 1 day before surgery. Patients will be evaluated on the morning of surgery, at discharge, and 1 month later. The primary outcome (anxiety) and secondary outcome (stoma adaptation) will be assessed at different time points. All phases of the study followed the Consolidated Standards for Reporting Trials (CONSORT) standards and the SPIRIT Checklist (Boutron et al. 2017). The planned participant flow of the study is presented in the CONSORT flowchart (Figure 1).

**FIGURE 1 nop270682-fig-0001:**
[figure not shown]
CONSORT flowchart.

### Inclusion Procedure

3.3

Participants will be recruited from an advanced medical faculty hospital that accepts patients from different regions of the country. Patients scheduled for stoma surgery will be identified by the responsible nurse and stoma care nurse working in the general surgery service of the hospital. The nurses will bring the researchers together with the patients who meet the study criteria and are scheduled for stoma surgery. Patients will be informed about the study by the researchers. Written informed consent will be obtained from the patients willing to participate in the study. At the same time, the researcher's contact information will be left with the patients, and they will be able to contact them at any time in case of difficulties they encounter.

### Participants'

3.4

#### Inclusion Criteria

3.4.1

The following patients were included in the study:
Those who are between the ages of 18 and 65.Who can speak Turkish.Who can read and write.Who is conscious.Who is willing to participate in the study?

#### Exclusion Criteria

3.4.2

The following patients were excluded from the study:
Those who are impaired in speech or hearing.Those with urostomy surgery.Those who need intensive care after surgery.Those whose stoma was closed during the study.Those who have had complications in the peristomal area.Those who had undergone stoma surgery before.Because conditions or medications that could independently affect anxiety levels, which is the primary outcome of the study, individuals with a diagnosed psychiatric disorder or who are currently taking psychiatric medication will not be included in the study.

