### Sample

3.5

The study will be conducted in an advanced hospital where approximately 9–12 stoma surgeries are performed monthly. The sample size was calculated using G*Power 3.1.9.2. The calculation was based on the primary outcome of the study, state anxiety. The effect size was calculated using the State Anxiety Inventory scores reported by Akbayrak and Uslu (2026), who evaluated the effect of preoperative stoma education including a wearable dummy stoma on postoperative stoma‐related anxiety, adjustment, and self‐efficacy. In that study, the mean State Anxiety Inventory scores were 36.24 ± 8.15 in the experimental group and 48.16 ± 10.14 in the control group. Based on these values, the effect size was calculated as *d* = 1.29. Using a two‐tailed independent‐samples *t* test, *α* = 0.05, power (1 − *β*) = 0.99, effect size = 1.29, and an allocation ratio of 1:1, the minimum required sample size was calculated as 46 participants, with 23 participants in each group. Considering a possible 10% attrition rate during follow‐up, including stoma closure, mortality, or participant withdrawal, the total planned sample size was increased to 52 participants, with 26 participants in each group.

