### Randomization

3.6

Participants who meet the eligibility criteria and provide written informed consent will be randomly assigned to either the intervention group (*n* = 26) or the control group (*n* = 26) in a 1:1 allocation ratio. A computer‐generated block randomization method with a fixed block size of four will be used to ensure balanced allocation throughout the study.

The randomization sequence will be generated before participant recruitment by an independent researcher who will not be involved in participant recruitment, intervention delivery, outcome assessment, or data analysis.

To ensure allocation concealment, the group assignments will be placed in sequentially numbered, opaque, sealed envelopes prepared by the independent researcher. After participant enrolment and completion of baseline assessments, the intervention researcher will open the next envelope in sequence to determine group allocation. This procedure will be implemented to minimize selection bias and preserve the integrity of the randomization process.

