#### Intervention Group

3.8.2

The stoma care nurse will inform the researcher, who will perform the application of the patients who meet the study criteria. In addition, the stoma care nurse will mark the area where the stoma will be opened with a surgical skin marking pen that is nontoxic, iodine‐free, resistant to rubbing, easy to dry, and suitable for surgical interventions. In addition to routine preoperative care and standard stoma education, patients in the intervention group will receive a stoma simulation intervention. Throughout the study, potential side effects related to the intervention (such as skin irritation, physical discomfort, or psychological distress) will be monitored. If any adverse events occur, the participant will be evaluated by the clinical team, and appropriate support will be provided when necessary. All adverse events will be recorded and reported by the researchers. If serious physical or psychological adverse events related to the intervention are observed, the participant's involvement in the intervention will be discontinued, and the study process will be re‐evaluated by the researchers. For the patients in the intervention group, the researcher will measure their state and trait anxiety levels after informing them about the study and providing written informed consent. A preprepared stoma bag containing wet napkins (information about the contents will be given but not shown to the patients) will be attached to the patient. When the stoma bag is attached to the patient, care will be taken to ensure that it is in the area marked by the stoma nurse. The adapter will be cut into an estimated stoma size, heated by friction of the hands, and adapted to the skin by applying stoma paste. The patient will be asked to put his/her hand on the adapter and apply pressure. Then, the stoma bag is filled with napkins and water, and the adapter will be combined. The patient will be informed that he/she should not hesitate to perform any activity with the stoma bag for 24 h. The patient will be allowed to go to the toilet, eat, sleep, and perform all daily activities with the stoma bag. Brava Adhesive Remover, spray, and Brava Adhesive Remover wipes will be used to clean the adapter adhesives and stoma paste residues on the morning of surgery. The patient's state of anxiety will be measured after the removal of the stoma bag. During the adaptation and removal of the stoma bag to the skin, the steps described in the literature will be followed (American Cancer Society 2019; Kirkland‐Kyhn et al. 2018). It may take time for patients who have had a stoma to adapt. Long‐term follow‐up is necessary for the study results to be more effective. In the literature, evaluating stoma adaptation in patients approximately 1 month after surgery is considered appropriate (Taylan and Aksoy 2021; Zhang et al. 2019; Whiteley et al. 2024). For this reason, stoma adaptations of patients will be evaluated at the time of discharge and 1 month after surgery. If patients have a possible problem with the stoma bag at night before surgery or have questions they want to ask, the information of the 24/7 open phone number where they can contact the researchers will be shared.

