### Evaluation of the Data

3.11

The data obtained from the study will be analysed using SPSS 21 (Statistical Package for the Social Sciences) software. First, the demographic and clinical characteristics of the participants will be summarized using descriptive statistics (frequencies, percentages, means and standard deviations). To assess baseline comparability between groups, independent‐samples *t* test will be used for normally distributed continuous variables, Mann–Whitney *U* tests for non‐normally distributed continuous variables, and chi‐square tests for categorical variables.

The primary outcome of the study is state anxiety measured using the State Anxiety Inventory. Changes in state anxiety scores between the intervention and control groups over time will be evaluated using repeated‐measures analysis of variance (ANOVA), including group, time, and group‐time interaction effects. The secondary outcome of the study is postoperative stoma adaptation measured using the Ostomy Adjustment Inventory. Changes in stoma adaptation scores between groups and across follow‐up measurements will also be evaluated using repeated‐measures ANOVA.

Age, gender, diagnosis, stoma type, baseline trait anxiety scores and baseline state anxiety scores will be prespecified as potential covariates. Baseline comparability between groups will be assessed, and adjusted analyses will be performed where clinically relevant imbalances are identified.

All primary analyses will be conducted according to the intention‐to‐treat (ITT) principle. Missing outcome data will be handled using multiple imputation methods. In addition, a per‐protocol analysis including participants who complete all planned assessments will be conducted as a sensitivity analysis. A significance level of *p* < 0.05 will be accepted in all analyses.

Every effort will be made to minimize missing data throughout the study. Reasons for missing data, participant withdrawals, mortality, and stoma closure will be documented and reported in detail. Results will be reported with 95% confidence intervals, effect sizes, and *p* values. The clinical significance of the findings will also be emphasized.

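### Section 3.4.2 lists as exclusion criteria events that arise after randomisation; applying them would contradict the intention-to-treat analysis in 3.11 and the handling of stoma closure in 3.5, 3.11 and section 5

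*Protocol article*

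**What the plan says.** Section 3.4.2 (Exclusion Criteria) lists "Those who need intensive care after surgery.Those whose stoma was closed during the study.Those who have had complications in the peristomal area". The same list bars "Those who had undergone stoma surgery before".

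The order of events is fixed elsewhere:

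- Allocation (3.6): "After participant enrolment and completion of baseline assessments, the intervention researcher will open the next envelope in sequence to determine group allocation".
- Simulation (3.2): "The application will be performed 1 day before surgery".
- Final primary measurement, morning of surgery (3.8.2, and 3.9 for the data collection schedule): "The patient's state of anxiety will be measured after the removal of the stoma bag".
- Adaptation, the secondary outcome, is measured at discharge and at 1 month (3.9 and Table 1).

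On analysis, 3.11 states: "All primary analyses will be conducted according to the intention‐to‐treat (ITT) principle". Missing outcomes are to be multiply imputed. A per-protocol set of patients who complete all assessments serves only as a sensitivity analysis. Stoma closure is to be documented and reported together with withdrawals and deaths.

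Section 3.5 adds a 10% attrition allowance, "including stoma closure, mortality, or participant withdrawal". Section 5 (Limitations) again names closure as a source of missing data.

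**The concern.** An eligibility criterion has to be decidable when the patient enters the trial. These three describe what happens to the patient at or after surgery, by which time the patient has been randomised and, in one arm, has received the simulation. They can then act only as removals after randomisation, and 3.11 promises an analysis without such removals.

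The two outcomes are exposed differently. For state anxiety, both measurements are complete before surgery begins, so removing a patient for a later event discards good data with no missingness to justify it. For stoma adaptation, patients with complications or a difficult recovery would drop out of the comparison. If the intervention changes who has these events, the remaining groups are no longer comparable. The Background (section 2) names inadequate preoperative preparation and poorly managed anxiety among the contributors to complications. The simulation is aimed at both, so unequal event rates are plausible, though not shown.

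**Working it through.** **1. Timing of each criterion against randomisation**

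| Criterion in 3.4.2 | Knowable before allocation? | Reason |
|---|---|---|
| Stoma closed during the study | No | The stoma does not exist until the trial surgery |
| Peristomal complications | No | Earlier stoma surgery is itself an exclusion, so there is no peristomal area at enrolment |
| Intensive care after surgery | Only if already planned | The wording is not limited to planned care |

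**2. How closure is classified:** exclusion in 3.4.2; attrition in 3.5; an event documented alongside missing data in 3.11; a cause of missing data in section 5. These cannot all govern the same patient. Intensive care and peristomal complications are not named in the attrition or missing-data text.

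**3. The protocol's sample size, reproduced.** Inputs from 3.5: means 36.24 (SD 8.15) and 48.16 (SD 10.14), two-sided alpha 0.05, power 0.99, ratio 1:1.

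- Pooled SD = √[(8.15² + 10.14²)/2] = √84.62 = 9.199.
- d = (48.16 − 36.24)/9.199 = 11.92/9.199 = 1.296 (stated as 1.29).
- Power at 23 per arm, noncentral t: 0.9898 for d = 1.29 and 0.9903 for d = 1.296.
- 46/0.9 = 51.1, giving 52.

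The stated 46 and 52 reproduce, so the sample size arithmetic is not at fault.

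**4. Power if the criteria were applied.** The documents give no rate for these three events, so the removal fractions are assumptions. Two-sided t test, noncentrality d√(n/2), d = 1.29:

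| Removed | n per arm | Power |
|---|---|---|
| 0 | 26 | 0.995 |
| 10% | 23 | 0.990 |
| 20% | 21 | 0.983 |
| 30% | 18 | 0.964 |
| One third | 17 | 0.954 |
| 40% | 16 | 0.942 |

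**5. Bias in the adaptation comparison, illustrated.** Suppose there is no true effect, the adaptation score has correlation ρ in size with a latent risk of the excluding events (higher risk, lower score), and the fraction p at highest risk is removed. The retained mean then rises by ρ·φ(z_p)/(1 − p) SD, where z_p is the normal quantile of p and φ the normal density. The factor φ(z_p)/(1 − p) is 0.195, 0.350, 0.497 and 0.644 for p = 0.1, 0.2, 0.3 and 0.4.

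| Removed, control vs intervention | Shift, ρ = 0.3 | Shift, ρ = 0.5 |
|---|---|---|
| 20% vs 20% | 0 | 0 |
| 30% vs 20% | 0.04 SD | 0.07 SD |
| 30% vs 10% | 0.09 SD | 0.15 SD |
| 40% vs 20% | 0.09 SD | 0.15 SD |

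In this model the shift favours the arm that loses more patients. If the simulation did reduce complications, the exclusions would work against it. The correlations and removal rates are assumptions.

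**The case against.** The strongest reply is that 3.4.2 concerns eligibility and 3.11 governs analysis. No section says outright that a randomised patient leaves the intention-to-treat set, and 3.11 can be read as keeping closures through imputation. That much stands: deletion follows from applying 3.4.2 and is not a stated analysis step. The two sections still conflict, and the imputation reading leaves intensive care and peristomal complications unaddressed.

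It is also fair that planned intensive care can be foreseen, so that criterion may need narrowing rather than deleting. The attrition causes in 3.5 are introduced as examples, so the absence of two events from that list proves little by itself.

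A reader might infer three stronger claims that the documents do not support:

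- *Most of the sample would be lost.* The Background says that stoma-related "complications account for an average of" two thirds of cases. That covers all stoma complications, with no time window, whereas this trial follows patients for about a month. Two-thirds removal would leave 8 to 9 per arm (power 0.67 to 0.73 at d = 1.29), but it is an upper bound and not an estimate for these criteria.
- *Site marking makes the exclusions unequal.* Marking is mentioned only under the intervention group (3.8.2), but it is done by the stoma care nurse, and 3.8.3 gives controls routine care from a clinical nurse and the stoma care nurse, withholding only the simulation. This does not show that controls go unmarked.
- *Skin irritation from the simulation would trigger exclusion.* The bag comes off before a stoma exists, and 3.8.2 routes irritation through adverse-event recording.

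**Conclusion.** The criteria are wrong as written. Stoma closure and peristomal complications, and intensive care unless planned, can only be established after allocation. If 3.4.2 is followed, the result is not the intention-to-treat result that 3.11 promises; if it is not followed, the eligibility section misstates who is in the trial. This rests on the protocol's own sequence of events and needs no assumed rate.

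The main harm is bias and a false intention-to-treat label, and it is greatest for adaptation. The illustrated shift is 0.04 to 0.15 SD when removal differs between arms by 10 to 20 percentage points, and nil in that model when removal is equal. For anxiety, the harm is the needless loss of complete data. Loss of power is secondary: at the planned effect size it stays above 0.94 up to 40% removal. That figure depends on d = 1.29 being true.

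**What to change.** - In 3.4.2, limit the exclusion criteria to facts known before randomisation, and reconcile the section with 3.5, 3.11 and section 5 so that closure has one status.
- State that no randomised participant is removed from the intention-to-treat set for an event after allocation.
- Keep all randomised participants in the anxiety analysis, with missing scores imputed as 3.11 already provides. Do not restrict it to those with a morning score; that complete-case rule would be weaker than the current plan.
- Continue to collect the Ostomy Adjustment Inventory after intensive care or peristomal complications where the patient still has a stoma.
- Treat closure and death as intercurrent events with a stated strategy for the adaptation outcome. Imputing an adaptation score for a patient who has died or no longer has a stoma needs a justification that the plan does not give.
- Report intensive care, closure and peristomal complications by arm.

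The cost is a protocol amendment, follow-up of some patients who would otherwise have been dropped, and somewhat more variable adaptation scores. The planned 52 need not change. Recruitment is planned to start on January 2, 2027 (3.1), and the amendment should be in place before then.
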